## Abstract

Rising temperatures in Africa present an increasing threat to agricultural productivity and public health, particularly among subsistence farming communities reliant on rain-fed agriculture. Heat exposure can impair farmers’ work capacity, disrupt harvests, and heighten health risks, especially for young children vulnerable to undernutrition. The Heat to Harvest (H2H) study investigates how environmental heat exposure influences farmers’ physiological and behavioral responses, and how these in turn affect harvest yields and child nutrition. It also examines differences in labor performance and recovery between households with and without cool roof coatings, although this intervention is not the central focus. H2H is designed as a prospective cohort study nested within two Health and Demographic Surveillance Systems (HDSS) in Nouna, Burkina Faso, and Siaya, Kenya. The study integrates environmental monitoring (temperature and humidity sensors used to compute Wet Bulb Globe Temperature), biometric data (via wearables tracking heart rate, temperature, physical activity, energy expenditure, and sleep), and GPS tracking (capturing spatial mobility and labor duration). The study is embedded within a larger cluster-randomized controlled trial, facilitating comparative analysis under varying thermal conditions. Findings will provide evidence-based insights into how climate-related heat stress affects health and agricultural outcomes, supporting the development of targeted adaptation strategies to enhance resilience, health, and food security in vulnerable farming communities.

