A sample size of 63 participants per group is estimated to detect a mean difference of 5 bpm in heart rate with 95% confidence and 80% statistical power. To accommodate potential attrition and inter-individual variability, the H2H study will enroll a total of 210 participants across 25 villages within the HDSS sites during the feasibility phase.

In the Nouna HDSS, the H2H study is nested within a cluster randomized controlled trial (cRCT) evaluating the effectiveness of cool roof coatings as a passive home cooling intervention (DRKS trials registry number DRKS00023207) [46]. Cool roof coatings are designed to reflect solar radiation and exhibit high thermal emittance, thereby reducing indoor temperatures [47].

The cRCT includes 600 households, with 300 households randomly assigned to receive the cool roof intervention and 300 serving as controls. For the H2H study, farmers will be equally sampled from both intervention and control households to ensure balanced exposure conditions. The H2H study does not treat the cool roof intervention as a direct proxy for heat exposure but considers it a potential modifier of recovery following occupational heat stress.

This nested design facilitates the investigation of both direct and indirect heat-related pathways [1]: direct exposure during agricultural work – analyzing physiological responses, work capacity, and productivity; and [2] post-exposure recovery at home, examining whether improved indoor thermal environments enhance recuperation and influence subsequent health and labour outcomes.

While the cool roof cRCT focuses on the effectiveness of home cooling, the H2H study is primarily concerned with occupational heat exposure. Nevertheless, the interaction between workplace heat stress and home-based recovery conditions is a central component in understanding the cumulative effects of heat on health and productivity over time.

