#### Heat – outdoor and indoor temperatures and humidity (health impact pathway 1)

To evaluate how housing characteristics and microclimatic conditions influence individual heat exposure, we will conduct a descriptive analysis of indoor and outdoor temperature and humidity, with a particular focus on differences between households with and without cool roofs. This analysis will quantify thermal and humidity gradients across housing types and environments, offering insight into how structural factors influence indoor microclimates and outdoor heat stress conditions.

To ensure a comprehensive characterization of environmental exposure, the following components will be examined:
Daily and seasonal temperature fluctuations, enabling the identification of peak heat stress periods across the agricultural calendar.Indoor – outdoor temperature and humidity differentials, stratified by roof type, ventilation characteristics, and other household attributes, to assess how built environments mediate exposure.The influence of humidity, which plays a critical role in perceived heat stress and modulates physiological responses, especially under high ambient temperatures.

These environmental variables will be statistically summarized using measures of central tendency and dispersion (mean, median, standard deviation, interquartile range), and visualized via time series plots, box plots, and heat maps. Stratified comparisons will also be conducted by region, household type, and season to identify spatial and temporal patterns in heat exposure.

Findings from this microclimate analysis will be integrated into the broader analytical framework (see Figure 5 and Table 1), enabling linkage of environmental conditions with outcomes such as physiological strain, labor capacity, and agricultural productivity. This component is essential for informing both the SEM-based mediation models (Section 2.5.1) and the machine learning approaches (Section 2.5.2), providing environmental context for predictive modeling.

In addition, we will assess how natural variability in environmental parameters – including diurnal temperature ranges, humidity shifts, and extreme weather events – contributes to heat stress dynamics. These factors will be included as covariates or interaction terms in regression and SEM models, ensuring that environmental heterogeneity is appropriately accounted for in downstream analyses of heat-related impacts.

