Additionally, we will analyze morning travel distances between participant households and agricultural plots – both Euclidean (straight-line) and actual walking paths – to estimate variation in daily physical exertion. These spatial metrics will be evaluated in relation to ambient and nighttime temperatures, providing further insights into how environmental stressors influence the following day’s physiological readiness and labor performance.

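### The article promises a comparison of labour and recovery by cool-roof status, but its analysis compares only indoor and outdoor climate by roof and relates recovery outcomes to measured temperatures, without using the randomised arm

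*Protocol article*

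**What the plan says.** **The objective.** The Abstract states: "It also examines differences in labor performance and recovery between households with and without cool roof coatings, although this intervention is not the central focus". Under Study participants and sample size, the article says that H2H does not use the roof as a proxy for heat exposure but "considers it a potential modifier of recovery following occupational heat stress". The same section describes a second pathway, post-exposure recovery at home, as "examining whether improved indoor thermal environments enhance recuperation and influence subsequent health and labour outcomes". It adds that "the interaction between workplace heat stress and home-based recovery conditions is a central component in understanding the cumulative effects of heat".

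**The contrast available.** In Nouna, H2H is nested in a cluster-randomised trial of 600 households, 300 allocated to cool roofs and 300 to control. H2H farmers are drawn equally from the two arms.

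**The analysis.** Under Data analysis, cool roofs are named in the pathway 1 subsection: "we will conduct a descriptive analysis of indoor and outdoor temperature and humidity, with a particular focus on differences between households with and without cool" (the quote stops one word short of the end of the phrase). The pathway 2 subsection puts indoor and outdoor temperature, humidity and WBGT into linear mixed models for heart rate, activity and sleep. Those models have individual-level random effects and covariates such as socioeconomic status and farming intensity. It then takes morning distances from home to plot, straight-line and walked, and says: "These spatial metrics will be evaluated in relation to ambient and nighttime temperatures". That is the article's analysis of the following day's readiness and labour.

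**The concern.** The stated question is whether labour and recovery differ by roof status, and whether the roof modifies recovery after a hot working day. The named analyses answer two different questions: whether homes with cool roofs have a different indoor climate, and whether measured temperatures are associated with physiology, sleep and travel distance.

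The second is observational. Indoor temperature follows outdoor weather, and between homes it also follows construction and wealth, which can affect sleep, workload and health by other routes. Random allocation of the roof shifts indoor temperature independently, in expectation, of weather, housing and wealth. It is the one randomised contrast in an otherwise observational cohort, and no outcome analysis is said to use it.

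Followed as written, the study could report that coated homes are cooler and that warmer homes or nights go with different sleep or next-day behaviour. Neither result would show that cooler homes improve recovery.

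**Working it through.** No arithmetic decides this point. The check is to set the objective beside each analysis, and then to ask how precise the missing contrast could be.

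**1. Where the roof appears in Data analysis**

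| Subsection | Outcome | Heat or roof variable | Roof arm named? |
|---|---|---|---|
| SEM and mediation | Physiological stress, work capacity, yield, child nutrition | Heat exposure | No |
| Advanced analytical methods | Physiological stress, child nutrition, time series | Indoor and ambient temperature | No |
| Pathway 1 | Temperature and humidity | Roof status, ventilation, other household attributes | Yes, descriptively |
| Pathway 2, mixed models | Heart rate, activity, sleep | Measured indoor and outdoor temperature, humidity, WBGT | No |
| Pathway 2, travel distance | Morning home-to-plot distance | Ambient and night temperature | No |
| Pathway 3 | Yield | Indoor and outdoor temperature, weather | No |
| Pathway 4 | Stunting, wasting | Heat exposure | No |

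Pathway 1 also promises covariates or interaction terms in the regression and SEM models. The factors it lists are diurnal temperature range, humidity shifts and extreme weather; roof allocation is not among them.

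**2. What the temperature analyses can show about recovery.** The mixed models bear on recovery, because they relate indoor temperature to sleep and heart rate. Adjusting for socioeconomic status addresses part of the between-household confounding. An individual random effect handles repeated measures but does not by itself remove between-household confounding. The travel-distance analysis is weaker. For a given home and plot the straight-line distance is fixed by geography, so a poor night cannot change it unless the farmer goes to a different plot.

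**3. Precision of a roof contrast (illustration).** The article's own figure is 63 per group for 5 bpm at 95% confidence and 80% power. It gives no SD. With an SD of 10 bpm the formula gives 2 × (1.96 + 0.84)² × 10² / 5² = 62.7, rounded up to 63, so about 10 bpm is implied. The two groups in that formula are not named, so it cannot be read as planning the roof comparison.

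The 210 participants span both sites and no split is given. For a simple arm difference, the smallest difference detectable with 80% power is (1.96 + 0.84) × 10 × √(2 × DE / n), with n per arm. The design effect is DE = 1 + (m − 1) × ICC. I assume m = 210 / 25 = 8.4 per village and a range of ICCs, since the article gives neither an ICC nor the trial's unit of randomisation.

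| Assumed Nouna share | n per arm | ICC 0 (DE 1.00) | ICC 0.05 (DE 1.37) | ICC 0.10 (DE 1.74) |
|---|---|---|---|---|
| All 210 | 105 | 3.87 bpm | 4.53 bpm | 5.10 bpm |
| About half | 52 | 5.49 bpm | 6.43 bpm | 7.25 bpm |

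Power for 5 bpm runs from 95% (105 per arm, ICC 0) to 49% (52 per arm, ICC 0.10). These figures treat each farmer as one value and cover the main arm difference only. The precision of the arm by work-heat interaction depends on within-person variation that the article does not give.

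**The case against.** **An article condenses the plan.** Secondary model terms are often left to a full protocol or SAP, and nothing here excludes an arm term. That stands as a caution: silence is not a decision to discard the randomised contrast. But the article goes pathway by pathway, and it places the roof comparison in pathway 1, as descriptive, with climate outcomes. That does not match the Abstract's labour and recovery comparison.

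**Recovery is analysed.** A reader might infer that home conditions receive only a descriptive treatment. They do not. The pathway 2 mixed models relate indoor temperature to heart rate, activity and sleep with socioeconomic adjustment, and the microclimate findings are to feed the wider framework. This objection stands. What remains is that the evidence is observational.

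**The roof is secondary.** A reader might take the article to call the roof comparison central. It does not: the words "the interaction between workplace heat stress and home-based recovery conditions is a central component" concern home recovery conditions. The Abstract says the roof is not the central focus, and none of the four hypotheses names it. A reader might also suppose that equal sampling by arm was chosen to study recovery. The purpose given is balanced exposure conditions.

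**The bias could be sized.** It is tempting to put a number on confounding of next-day work by same-day heat. The documents give no slope or correlation for this. The next-day outcome is travel distance, not hours worked, and ambient temperature is part of the analysis. No such figure is supported.

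**The contrast is imprecise and covers one country.** True. That limits the claim to an exploratory estimate with an interval, but it does not make the observational association a substitute for the randomised contrast.

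**Conclusion.** The mismatch holds in a limited form. The article says it examines labour and recovery by roof status and treats the roof as a possible modifier, but no analysis it names compares those outcomes by arm. The temperature models bear on recovery but remain open to confounding by housing and wealth that socioeconomic adjustment may not fully remove.

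The consequence is a stated secondary objective without a matching analysis. The primary question on occupational heat is unaffected. The amount of bias cannot be computed from the documents. The advantage claimed for the arm contrast assumes that farmers are sampled at random within arms, that consent does not differ materially by arm, and that households are analysed as allocated. The change is worth making because the arm is known and the outcome data are already planned.

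**What to change.** Add to the pathway 2 analysis, for Nouna participants only, an exploratory analysis of the roof as a modifier of recovery:

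- **Outcomes:** sleep duration and quality, night heart rate, and next-day time in the field.
- **Terms:** randomised roof arm, previous-day work heat, their interaction, and outdoor heat.
- **Random effects:** participant, and the parent trial's unit of randomisation, which the text should name.
- **Not included:** indoor temperature, because it is the route through which the roof would act.
- **Reporting:** arm differences and the interaction as estimates with confidence intervals, labelled exploratory and limited to Nouna.

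Keep the measured-temperature models and the travel-distance analysis as supportive evidence on recovery.

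If this analysis is not wanted, reword the Abstract and the sample-size section so that the roof objective is a descriptive comparison of indoor climate.

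The cost is analysis wording. Wearable heart rate and sleep, GPS field time and roof allocation need no new collection, although field time is assured for only the minimum of 20 GPS days a year. The downside is an interaction that will be imprecise and available in one country only.

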#### Harvest yields (health impact pathway 3)

To assess spatial variation in agricultural productivity and its relationship with heat exposure, we will conduct geospatial analyses using Geographic Information System (GIS) tools. Field boundaries – mapped via GPS – will be overlaid with remote sensing data to extract vegetation indices for each field, enabling a spatially explicit assessment of crop health and yield under varying environmental conditions.

Household-level agricultural production will be estimated using LASSO (Least Absolute Shrinkage and Selection Operator) regression models, incorporating variables such as crop type, phenological stages, and time-series vegetation indices – specifically the Normalized Difference Vegetation Index (NDVI), Normalized Difference Red Edge Index (NDRE), and Normalized Difference Water Index (NDWI) – derived from Sentinel-2 satellite imagery, as well as rainfall data from CHIRPS. To improve model robustness and prevent overfitting, five-fold cross-validation will be used to optimize model parameters and assess predictive performance.

Separate LASSO models will be developed for each major crop type, following established methods [31], thereby enhancing model specificity and improving yield forecasts at the field level. This modeling approach allows us to link remote sensing indicators to field-level agricultural output with high spatial and temporal resolution.

To evaluate the influence of heat exposure on productivity, we will identify and compare high- and low-yield regions in relation to spatial and temporal variations in temperature, integrating both indoor and outdoor temperature data. Additionally, fluctuations in temperature, humidity, and extreme weather events will be included in the analysis to assess their contributions to yield variability and to control for potential environmental confounders.

By embedding these geospatial analyses within the broader analytical framework, we aim to generate nuanced insights into how environmental stressors – particularly heat – affect agricultural output at the household level, and how this, in turn, may mediate impacts on work capacity and child nutrition.

#### Nutritional status (health impact pathway 4)

Anthropometric measurements, including weight and height assessments of children under five years of age, will be used to identify those with poor nutritional status. Nutritional classification will follow the World Health Organization (WHO) Child Growth Standards, where chronic undernutrition (stunting) is defined as a height-for-age z-score (HAZ) ≤ −2.0, and acute undernutrition (wasting) as a weight-for-height z-score (WHZ) ≤ −2.0, adjusted for age and sex [50].

To assess the relationship between heat exposure and child nutritional status, chi-square tests will first be used to evaluate unadjusted associations associations between categorical heat exposure levels and the prevalence of stunting and wasting. To estimate the independent effect of heat exposure on child growth outcomes, multivariate logistic regression models will be employed, adjusting for potential confounders such as household socioeconomic status, dietary intake, and recent illness episodes. To ensure the robustness of these findings, sensitivity analyses will be conducted to control for key confounding factors, including household socioeconomic status, dietary intake, and recent illness episodes. These additional analyses will allow for a more accurate estimation of the independent effect of heat exposure on child growth outcomes, strengthening causal inference within the broader analytical framework.

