
The health impacts of climate change are primarily driven by rising temperatures and increased heat exposure, which are projected to contribute to a surge in heat-related morbidity and mortality, including conditions such as heat stress, cardiovascular diseases, and renal dysfunction [9]. Additionally, climate change is expected to exacerbate the burden of communicable diseases such as dengue fever, pathogenic *Vibrio* infections, and malaria, as warmer and more humid conditions enhance the suitability for vector proliferation and disease transmission [9]. Changes in rainfall and temperature patterns are likely to affect mosquito breeding cycles, further increasing malaria risk [9]. Notably, malaria, pneumonia, and diarrheal diseases together account for nearly half of all deaths in children under five in sub-Saharan Africa (SSA) [27]. In the Kossi region of northwestern Burkina Faso, shifting seasonal weather patterns, rising temperatures, and extreme weather events, including heavy rainfall and flooding, have been associated with direct health impacts, including increased incidences of heatstroke and malaria, as well as indirect effects such as heightened food insecurity and child undernutrition [3,28–32]. In both Burkina Faso and Kenya, climate change exacerbates child undernutrition by compromising food security [30,33,34]. The increasing frequency of severe weather events, such as droughts and floods, reduces crop yields and elevates food prices, leading to inadequate dietary intake and heightened health risks associated with undernutrition [30,33,34]. Chronic undernutrition affects 26% of children under five in Burkina Faso and over 25% in Kenya, contributing to stunting, while acute undernutrition leads to wasting in about 7% of children in Burkina Faso and 4% in Kenya. These conditions have long-term consequences for cognitive and physical development [30]. Moreover, exposure to drought during late childhood and early adolescence has been shown to have persistent adverse effects on growth, primarily mediated by reduced nutritional intake during critical developmental years [35]. In Burkina Faso, studies have demonstrated that rainfall variability directly impacts crop yields and correlates with increased child undernutrition in affected households [36,37].

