**Figure 5. f0005:**
[figure not shown]
Overview of exposure and outcome variables within the Heat to Harvest (H2H) study, and their sequential and cascading framework.

**Table 1. t0001:** Overview of pathways, outcomes and exposure with corresponding measured variables.

	**Pathway**	**Measured variable**	**Functional form**
Exposure	Heat	– Indoor temperature and humidity	– continuous
		– Outdoor climate conditions (air temperature, rainfall, wind speed, wind direction, solar radiation, humidity)	– continuous
Outcome	Physiological response and work capacity	– Wearable data (heart rate, energy expenditure, activity levels, sleep)	– continuous
		– GPS data (farmers work itineraries and time allocation)	– spatiotemporal data
Outcome	Harvest yield	– Remote sensing data (vegetation indices)	– raster
		– Field boundaries measured with GPS devices (locations of crop fields)	– point data
Outcome	Nutritional status	– Anthropometric measurements (weight, height measurements of children < 5 years)	– continuous

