#### Structural equation modeling (SEM) and mediation analysis

To assess both direct and indirect effects of heat exposure, the study will employ Structural Equation Modeling (SEM) with mediation analysis. This approach enables the simultaneous estimation of multiple pathways linking heat exposure to physiological stress, work capacity, harvest yields, and child nutrition, providing a comprehensive understanding of the cascading impacts of heat stress.

Direct effects will be assessed by evaluating the independent influence of heat exposure on physiological stress (e.g. heart rate, energy expenditure), work capacity (e.g. labor duration, frequency of rest breaks), and child nutritional status. These analyses will offer insights into the immediate physiological and occupational impacts of heat and their direct links to health outcomes in children.

Beyond direct effects, SEM will estimate indirect pathways through which heat exposure impacts agricultural productivity and child nutrition. The central hypothesis posits that heat exposure induces physiological stress, which subsequently reduces work capacity, leading to decreased harvest yields and, ultimately, to poorer nutritional outcomes in children. Mediation will be tested using specific pathway models, such as:
Heat exposure → Physiological stress → Reduced work capacityHeat exposure → Reduced work capacity → Lower harvest yields → Poorer child nutrition

To quantify the role of mediating variables, indirect effects (e.g. via work capacity) will be compared with total effects (the overall impact of heat exposure on child nutrition), allowing for estimation of the relative contribution of different pathways.

To ensure the validity and robustness of the SEM, model fit will be assessed using multiple indices, including the Chi-square test, Comparative Fit Index (CFI), Tucker-Lewis Index (TLI), and Root Mean Square Error of Approximation (RMSEA). Through this rigorous analytical framework, the study aims to generate reliable and generalizable evidence on how heat stress affects the livelihoods and health of subsistence farming households.

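### The dedicated child-nutrition analysis uses only stunted/wasted yes-or-no outcomes and names no model of the continuous z-scores, at a large cost in precision for wasting and a moderate one for stunting

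*Protocol article*

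**What the plan says.** In the Data analysis part of the protocol article, the section Nutritional status (health impact pathway 4) defines stunting as "height-for-age z-score (HAZ) ≤ −2.0" and wasting as "weight-for-height z-score (WHZ) ≤ −2.0". It then names two analyses:

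- First, chi-square tests of unadjusted associations "between categorical heat exposure levels and the prevalence of stunting and wasting".
- Second, for the independent effect of heat, "multivariate logistic regression models will be employed, adjusting for potential confounders". The adjusters named are socioeconomic status, dietary intake and recent illness.

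The sensitivity analyses in the same section list the same three adjusters and do not change the outcome scale.

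Table 1 gives the functional form of each variable. It lists "Anthropometric measurements (weight, height measurements of children < 5 years") as continuous, and likewise indoor temperature and humidity and "Outdoor climate conditions (air temperature, rainfall, wind speed, wind direction, solar radiation, humidity").

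Child nutrition also enters the structural equation model (SEM), which is meant for "simultaneous estimation of multiple pathways linking heat exposure to physiological stress, work capacity, harvest yields, and child nutrition", and the neural networks under Advanced analytical methods. Neither section states whether nutrition is modelled as a z-score or as a yes/no variable. On prevalence, the Background says that "acute undernutrition leads to wasting in about 7% of children in Burkina Faso and 4% in Kenya", and puts stunting at 26% and just over 25%.

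**The concern.** Cutting a z-score at −2.0 treats all children on the same side of the line as identical. A child whose z-score falls from −0.5 to −1.5 contributes nothing to either named analysis. The loss grows as the cut-off moves into the tail, so it is worst for wasting, the rarer condition. If heat is cut into categories as well, more is lost.

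What is at stake is the precision of the heat–nutrition estimate, the last link in the causal chain that the study sets out to describe. A weak or null result for wasting could reflect the coding of the outcome rather than the absence of an effect. Few wasted children would also make an adjusted logistic model imprecise. The loss is avoidable: the z-scores have to be computed before they can be cut, and linear mixed models are already planned for the farmers' continuous outcomes under pathway 2.

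**Working it through.** **The plan's own figure.** The only sample size is 63 per group, for a 5 bpm difference in heart rate. It is recovered as 2 × (1.96 + 0.84)² × 10² / 5² = 62.7, rounded up to 63, if the SD is 10 (an assumption, since the document gives no value). It says nothing about child nutrition, for which no sample size or power is stated.

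**Information kept by the yes/no outcome.** For a small shift in a normal variable, a cut that classes a proportion *p* as cases has relative efficiency φ(z_p)² / [p(1 − p)]. Here z_p is the normal quantile and φ the normal density. Prevalences are from the Background.

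| Outcome | p | z_p | φ(z_p) | φ² | p(1 − p) | Kept |
|---|---|---|---|---|---|---|
| Wasting, Kenya | 0.04 | −1.751 | 0.0862 | 0.00743 | 0.0384 | 0.19 |
| Wasting, Burkina Faso | 0.07 | −1.476 | 0.1343 | 0.01803 | 0.0651 | 0.28 |
| Stunting, Kenya | 0.25 | −0.674 | 0.3178 | 0.10098 | 0.1875 | 0.54 |
| Stunting, Burkina Faso | 0.26 | −0.643 | 0.3244 | 0.10521 | 0.1924 | 0.55 |

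The yes/no outcome alone therefore loses 72–81% for wasting and about 45% for stunting.

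**Adding categorised heat (chi-square step only).** The categories are not defined, so a range is needed. Cutting a normal exposure into equal groups keeps 0.64 (two groups), 0.79 (three), 0.86 (four) or 0.90 (five). Multiplied by the figures above, the chi-square step keeps 0.12–0.25 for wasting and 0.34–0.49 for stunting.

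**In sample-size terms.** Take an illustrative 0.3 SD difference between two groups, 80% power, two-sided 5%:

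- Continuous z-score: 2 × 2.8² / 0.3² = 174.2, so 175 per group.
- Stunting at 26% (31.1% against 21.4%): 322 per group.
- Wasting at 7% (9.2% against 5.2%): 642 per group.
- Wasting at 4% (5.5% against 2.9%): 924 per group.

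**Simulation at N = 210**, with an effect that has about 80% power when both variables are continuous:

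| Analysis | Stunting, 26% | Wasting, 7% |
|---|---|---|
| Logistic, continuous heat | 56% | 32% |
| Chi-square, heat split at median | 39% | 21% |
| Chi-square, heat in quartiles | 34% | 16% |

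**Number of wasted children.** The number of children is not stated. Assume one child per enrolled farmer and one measurement round:

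- 210 × 0.04 = 8.4 to 210 × 0.07 = 14.7 wasted. With equal sites, 105 × 0.07 + 105 × 0.04 = 11.6.
- With heat plus three adjusters (at least four parameters), that is 8.4/4 = 2.1 to 14.7/4 = 3.7 events per parameter.
- The standard error of the log odds ratio per SD of heat is at best about 1/√[N p(1 − p)]: 1/√(210 × 0.0651) = 0.27 at 7% and 1/√(210 × 0.0384) = 0.35 at 4%. The 95% interval then runs from the estimate divided by, to the estimate multiplied by, exp(1.96 × 0.27) = 1.7 or exp(1.96 × 0.35) = 2.0. Correlated covariates would widen it.

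If children are measured in each of three years, 630 records would give 630 × 0.04 = 25 to 630 × 0.07 = 44 wasted records, correlated within child.

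**The case against.** Much can be said for the plan, and several stronger readings should be resisted.

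- **Exposure–response functions.** A reader might infer that the functions promised under Expected results cannot be obtained. The text does not support this. Categorical heat is mentioned only for the first, unadjusted step. The scale of heat in the logistic models is not stated, and a logistic model with continuous heat does yield an exposure–response function.
- **Most of the information lost throughout.** This holds for wasting, and for stunting only in the chi-square step. The yes/no stunting outcome alone keeps just over half.
- **Nutrition analysed only as yes/no.** The SEM and the neural networks also model it, and the mediated effects in Hypothesis 4 belong to the SEM. Continuous nutrition there would agree with Table 1. But the scale is not stated, so this does not settle the matter.
- **A wasting model that fails.** The count of 8–15 rests on one child per farmer and one round. More children or repeated rounds would raise it. Simulated four-predictor logistic models at N = 210 failed to converge or separated in a small share of runs: about 8% at most, at 4% prevalence, and fewer at higher prevalence. Imprecision is the expected result, not failure.
- **Legitimate cut-offs.** Growth-standard thresholds are a proper way to report stunting and wasting. If heat acted mainly on children near the threshold, the cut would lose less than calculated here.
- **Priority.** Heart rate is the primary outcome and this is a feasibility phase. Undefined heat categories are a detail that an article may leave to the analysis plan.

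These points narrow the concern. They do not supply a model of the continuous z-scores in the section devoted to pathway 4.

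**Conclusion.** The point holds in limited form. Both named pathway-4 analyses dichotomise the z-scores, no continuous model is named, and Table 1 classes the same measurements as continuous. The yes/no outcome keeps about 19–28% of the information for wasting and 54–55% for stunting, and the chi-square step keeps less. These fractions assume normal z-scores and a small shift in their mean, and they do not depend on the number of children. The statement that an adjusted wasting model would be imprecise does depend on that number, and on the single-round assumption.

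This is an inexpensive gain in precision for a secondary pathway. It does not invalidate the study, and it gives no ground for saying that exposure–response functions are out of reach or that the models will break down.

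**What to change.** In the section on nutritional status:

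- Make continuous height-for-age and weight-for-height z-scores the main pathway-4 outcomes, in linear mixed models with heat as a continuous exposure (a spline if the relation is not linear) and random effects for child or household and for village.
- State that the SEM uses the continuous z-scores.
- State the scale of heat in the logistic models. Keep those models, the stunting and wasting prevalences and any chi-square comparison as secondary or descriptive.
- State the expected number of children and measurement rounds, so that the expected number of wasted children can be judged.

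The cost is analysis wording and a modest amount of extra modelling, with no new data collection. Mean z-score differences are less direct for policy readers than prevalence, but prevalence would still be reported.
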